# Optimising symptom management in children with cancer using a novel mobile phone application: protocol for a controlled hybrid effectiveness implementation trial (RESPONSE)

**DOI:** 10.1186/s12913-021-06943-x

**Published:** 2021-09-09

**Keywords:** Child, Adolescent, Cancer, Patient Reported Outcome, Digital health, Mobile health, Symptoms and side effect, Health services research, Implementation, Trial

## Abstract

**Background:**

Intense and aggressive treatment regimens for most children’s cancer have achieved vast improvements in survival but are also responsible for both a high number and burden of symptoms. The use of Patient Reported Outcome Measures (PROMs) demonstrates a range of benefits for improved symptom management in adults with cancer. There are, however, multiple barriers to integrating PROMs into routine care in children and adolescents with cancer. This study aims to evaluate: (1) the effectiveness of electronic PROMs to generate stratified alerts, symptom management recommendations and graphical summaries (the RESPONSE system) to improve health outcomes and (2) the implementation of the RESPONSE system by assessing feasibility, acceptability, satisfaction, and sustainability.

**Methods:**

A pragmatic hybrid II effectiveness-implementation controlled trial, using mixed methods, will be undertaken, advancing both knowledge of the effectiveness of the intervention and implementation factors. One-hundred and sixty children with cancer receiving active treatment will be recruited 1:1 to a non-randomised study involving two groups with an equal number of participants in each group. The intervention group (*n* = 80) will be prospectively recruited to receive the RESPONSE system intervention over eight weeks, versus the historical matched control group (*n* = 80) who will complete the ePROMs without access to the RESPONSE system. The primary outcome of the effectiveness trial is change between groups in total symptom burden. Secondary outcomes include child health-related quality-of-life and implementation outcomes. Trial data will be analysed using linear mixed-effects models. Formative implementation evaluation is informed by CFIR and ERIC frameworks and implementation outcomes will be mapped to the RE-AIM framework and include interviews, field notes, as well as administrative data to evaluate feasibility, acceptability, satisfaction and sustainability.

**Trial registration number:**

ACTRN12621001084875. Retrospectively Registered 16 August 2021.

## Background

Children undergoing treatment for cancer experience multiple, persistent and distressing symptoms related to cancer and treatment [1, 2]. Up to 30 % experience ten or more symptoms that persist up to two weeks following chemotherapy [3]. However, children and their caregivers may perceive this high symptom burden to be inevitable or even a sign that treatment is working, and thus may not report symptoms amenable to intervention [4]. Further to this, symptoms are also often undetected and undertreated by clinicians [5]. As more treatment is delivered in the ambulatory care setting, children often suffer symptoms at home, away from clinical care [6], resulting in perceptions that there are few options for intervention [7]. This limits opportunities for patients and caregivers to receive support and education from clinicians to manage symptoms effectively. Caregivers are expected to take on the responsibility of managing their child’s symptoms, yet there are few resources to support this, and they often report feeling left alone [8].

It is evident, that symptom management is sub-optimal, causing both unnecessary distress and avoidable hospitalisations [9]. Poor symptom control affects treatment tolerance and can cascade into longer-term problems that negatively impact both the child and their families’ quality-of-life [10–12]. Furthermore, poor symptom control is associated with poorer psychological outcomes [13] and PTSD that may not emerge for years following treatment [14]. New ways are needed to support children and their caregivers to communicate with healthcare providers and receive management recommendations about distressing symptoms, regardless of the setting in which care is provided.

The use of Patient Reported Outcome Measures (PROMs) in routine clinical care can overcome barriers by normalising symptom reporting processes, placing value on patient experience and generating timely, reliable data on which to act [4]. PROM responses about health come directly from the patient, their proxy, or in the case of children co-completion with the caregiver is advocated [15]. There is compelling evidence for the effectiveness of PROMs to improve quality of care, shared decision making, and communication at the individual level [16–18]. Additionally PROMs can improve health at the population level through reduced costs, and enhanced clinician satisfaction with work [19].

There are, however, multiple barriers to integrating PROMs into routine care for children at the individual, clinical, organisational and systems level [4]. At the individual level, the child’s developmental stage, their understanding of symptoms, and the availability of child-friendly measures present barriers. At the clinical level, outcomes that matter to healthcare providers (symptoms that delay treatment) may not be the same as those that matter to children (concerns with body image and feeling anxious) [2, 5]. Clinicians may also be concerned about resources, and the burden versus benefit value proposition [20]. From an organisational perspective, technological barriers prevent the integration of electronic data from PROMs (ePROMs) into clinical workflow processes, management plans and medical records, limiting feasibility and acceptability [16]. From a systems perspective, there is questionable financial incentive to integrate PROMs as well as uncertainty about implementation approaches; given the expense and logistical challenges, health services are understandably cautious [21].

These barriers and other implementation factors can be examined using tools from implementation science. Multiple frameworks guide the implementation evaluation of the intervention, which includes a systematic, formative and summative evaluation that considers the context, causal assumptions and mechanisms of impact. The elements and constructs from implementation frameworks are useful for mapping barriers to implementation, developing strategies to mitigate identified barries and also to evaluate the implementation outcomes; understanding all these phenomena can ultimately facilitate the sustainability and scalability of interventions [22, 23].

Accordingly, we report the protocol of a study to evaluate the effectiveness and implementation outcomes of an ePROM intervention targeting symptoms in children undergoing systemic cancer treatment – the RESPONSE system. The intervention involves multiple components including: (1) weekly monitoring of symptoms using a validated, child friendly ePROM (SSPedi) [24, 25]; (2) stratified alerts for symptoms that reach pre-determined thresholds requiring intervention; (3) evidence-based symptom management recommendations, and (4) graphical displays of SSPedi information enabling symptom trends to be visualised over time. The comparison intervention involves completion of ePROMs alone, without stratified alerts, symptom management recommendation or graphical displays.

## Methods and Design

### Aims and objectives

The primary aim is to determine the effectiveness of the RESPONSE system intervention on the total symptom burden of children receiving cancer treatment. Secondary aims are to assess effects on health-related quality-of -life and implementation outcomes.

### Hypothesis (effectiveness component)

The implementation of ePROMs, stratified alerts, provision of symptom management recommendations, and graphical displays using the RESPONSE system will reduce the total symptom burden experienced by children receiving treatment for childhood cancer compared to the ePROM alone intervention.

### Implementation outcomes

Implementation outcomes include the feasibility, acceptability, satisfaction and sustainability of implementing the RESPONSE system intervention. The contextual factors and core components of the intervention will be identified for inclusion in a future large-scale randomised controlled trial.

### Context and setting

The setting for the study is a children’s cancer centre at a major metropolitan hospital in Australia. The centre receives approximately 200 children newly diagnosed with cancer each year, and treatment can take up to three years or longer to complete. The catchment of the hospital includes rural, regional and metropolitan areas and has formal networks established with 12 smaller regional hospitals that provide supportive children’s cancer care. Caregivers (and their eligible child with cancer) will be consecutively approached and recruited to the study.

### Development of the intervention

The RESPONSE system was iteratively developed with clinicians, children and caregivers throughout 2019–2020. Firstly, a clinical reference group was established comprising 12 oncology medical, nursing and allied health staff who met at least monthly through intervention development. The first objective was to review available PROMs described in systematic reviews [6, 26, 27]. The SSPedi was chosen because of its ease of use with children, brevity and due to its intended use as a routine measure for symptom assessment, rather than as a proxy measure or end-point for other intervention studies [22, 24, 25]. SSPedi uses a 5-point Likert scale to measure the degree of bother either today or yesterday (0 = not at all − 4 = extremely bothered) for 15 different symptoms. The measure is validated for children 8–18 years, their caregiver proxy, and for ‘co-completion’ by both child (4–18 years) and caregiver together [15]. Cognitive interviews were completed with children and caregivers to confirm the content validity of SSPedi and its relevance to the Australian population [25].

### Stratified alerts, symptom management recommendations and graphical trends

The clinical reference group iteratively developed algorithms to determine thresholds for each of the 15 symptoms measured by SSPedi. Each symptom was individually appraised for the level of potential risk, with each possible answer of bother determining one of three responses regarding management. The algorithms include reference to previous SSPedi completion within the previous 14 days, as well as diagnosis. The final algorithms were ratified by oncologists, nursing and allied health staff at the children’s cancer centre.

Evidence-based symptom self-management recommendations were drafted from clinical practice guidelines (where available) by the clinical reference group and endorsed by medical, nursing and allied health oncology clinicians working in the study setting [28]. Recommendations were appraised for ease of reading, ensuring content was at an appropriate reading level (grade 8) or below. Wording was also reviewed by two adolescents (age 13 and 15 years) for content and language resulting in some changes. A consensus was obtained through discussion with the clinical reference group to graph SSPedi both for one-time completion (visualising all symptoms on a bar graph), as well as an option to select up to three symptoms to view over a 1-week, 4-week and 12-week time period. These time periods were chosen to correspond with common chemotherapy protocols in children’s cancer. All components were then incorporated into the design of a mobile application (app).

### Mobile Application Design

Along with digital technology experts and input from caregivers of children with cancer, a subgroup of the clinical reference group (n = 5) iteratively conceptualised and developed the design for the app. Wireframe screens were developed using online software, and these were presented to stakeholders, with feedback used to make modifications. Cognitive interviews were undertaken with nine caregivers and two adolescents with cancer using ‘think-aloud’ techniques in order to test the design of the app [29]. Changes to the design were made based upon feedback, such as including the use of more colour, wording and adding places for caregivers to record notes (Fig. 1).

**Fig. 1 Fig1:**
[figure not shown]
Screen shots of the RESPONSE mobile phone app

After caregivers register within the app and view the introductory welcome screens, the ePROM is completed by the participant by selecting the appropriate response corresponding to the level of bother for each symptom. After completion, the algorithm determines the stratified alert using a traffic light system: green - no concern; amber - concern that requires discussion with the clinical team at the next clinic visit, and red - concern that requires immediate discussion with the clinical team, with caregivers prompted to phone the hospital. Relevant symptom management recommendations are then presented within the app. Graphical displays of all symptoms can be viewed at any time.

Once the design of the app was completed, it was provided to the Information Communication Technology partner of the Children’s Hospital for development. The backend of the app database is stored on an approved secure and private cloud server within Australia, that meets the requirements for the protection of participants in relation to confidential processing, collection, and access to personal data. A web-based portal provides access for clinical staff to manage users, facilitate push notifications (for example, reminders to complete ePROMs) and tracking in a convenient format. While these data are available to clinicians, they are not linked to medical records and the RESPONSE system is designed as a caregiver and child patient-facing app, providing information directly to the user.

### Pre-implementation planning

Interviews were conducted with clinicians as part of the pre-implementation planning. Interview questions were informed by the Consolidated Framework for Implementation Research (CFIR) [30] (Table 1). Findings are used to iteratively develop, design and guide strategies for implementation using the ERIC Expert Recommendation for Implementing Change (ERIC) [31] compilation of strategies. The CFIR-ERIC Implementation Strategy Matching Tool was used to facilitate this process [23]. For example, we identified a potential barrier of nursing staff not having access to relevant information regarding evidence-based symptom management for all the symptoms screened with SSPedi. Accordingly, education modules were developed to support nursing symptom management education at novice, intermediate and advanced levels. To ensure organisational support, presentations of the project were made to oncology medical and nursing and allied health staff, hospital executives, the state-wide clinical networks, and the family centred care committee (Table 2).

**Table 1 Tab1:** Pre-implementation formative evaluation clinician interview questions

Interview questions to clinical staff	CFIR Domain
What is your understanding of the RESPONSE intervention to support symptom management in children with cancer?	CFIR/Characteristics of Individuals/Knowledge and Beliefs about the intervention
What is your understanding of how the intervention will be integrated into current practices?	CFIR/Inner Setting/Implementation Climate/Compatibility
Do you feel that you have the current knowledge level and skills to answer potential calls from caregivers regarding symptoms identified by the SSPedi Tool?	CFIR/Inner Setting/Readiness for Implementation/Access to knowledge and information
Do you think educating patient and /or caregivers in how to access and use the RESPONSE intervention is part of your role?	CFIR/Inner Setting/Implementation Climate/Relative Priority
Are there other initiatives in your workplace that have higher priority?	CFIR/Inner Setting/Implementation Climate/Relative Priority

*CFIR* Consolidated Framework for Implementation Research

**Table 2 Tab2:** CFIR-ERIC Implementation Strategy [23] examples

*CFIR Potential Barriers Identified*	*ERIC Strategies*
Intervention characteristics: • Stakeholders perception of RESPONSE intervention unclear • Stakeholders believe the innovation is complex based upon disruptiveness and number of steps needed to implement	• Assess for readiness an identify barriers and facilitators • Create a learning collaborative, tailor strategies, promote adaptability
Inner setting • Cultural norms, values and assumption may hinder implementation • There is little motivation for change, and no expectation that use of the innovation will be rewarded, supported or expected	• Involve Executive Boards • Inform local opinion leaders • Identify early adopters • Conduct local needs assessment • Designate and train for leadership
Process • Little or no quantitative and qualitative feedback about the progress and quality of implementation nor regular debriefing about progress and experience	• Audit and provide feedback • Develop and implement tools for quality monitoring • Develop formal implementation blueprint

*CFIR* Consolidated Framework for Implementation Research [30]

*ERIC* Expert Recommendation for Implementing Change compilation [31]

### Study design

A pragmatic hybrid II effectiveness-implementation, controlled trial and implementation study was designed to evaluate the RESPONSE system intervention. A hybrid design advances knowledge of both the effectiveness of the intervention and the implementation factors associated with integration into clinical practice [32]. This is the best available method to collect high-quality comparative data, and expedite findings and translation into clinical practice. For ethical reasons, a non-randomised design was chosen, as the children’s cancer centre endeavoured to make the app available to all children and families. Hence, a matched control group is being recruited during the development of the app; non-randomised controlled trials are commonly used in children’s cancer studies [33, 34]. An embedded process evaluation mapped to the RE-AIM framework [35] is included to assess implementation outcomes including acceptability, fidelity and satisfaction (Table 3). This involves interviews with caregiver and child participants as well as clinicians. It also involves collecting fields notes, and relevant clinical and administrative data.

**Table 3 Tab3:** Implementation outcome measures mapped to the RE-AIM framework [44]

Setting	RE-AIM domain	Data collected	Timing
*Primary outcome*:			
	**EFFECTIVENESS**		
Child/Caregiver	Total symptom burden	SSPedi	Weekly for 8 weeks
*Secondary outcomes*			
	**EFFECTIVENESS**		
Child/Caregiver	Health-related quality-of-life	PedsQL Cancer Module	Baseline, week 4, week 8
Child/Caregiver	Distress thermometer	Distress Thermometer	Baseline, week 4, week 8
QCH records	Economics- health service utilisation	Unplanned hospital admissions	Audit at completion
Child/Caregiver	Experience of care, acceptability, satisfaction	Semi-structured interviews	Completion of recruitment
	**REACH**		
QCH	Percentage uptake of RESPONSE system among eligible children	Log data from recruitment database	Audit at completion of recruitment
Medical record	Percentage of eligible children recruited Clinical and demographic characteristics	Log data from recruitment database	At recruitment
Service providers	Proportion of staff reached by educational presentations	Structured interview	At completion of data collection
	**ADOPTION AND MAINTENANCE**		
Child/Caregiver and Health care providers	% eligible children/caregivers/ healthcare providers educated to use RESPONSE system	Log data from intervention database	Audit at completion of recruitment
Service providers	% aware of RESPONSE system% use RESPONSE data in clinical consultations	Log data from intervention database	Audit at completion of data collection
Child/Caregiver	Fidelity to protocol	Data from intervention database	Audit at completion of data collection
Child/Caregiver	Number of links to management recommendation opened	Dashboard for app	Audit of app data at completion
Service providersChild medical records	Number of alert generated contacts receivedNumber of interventions/ referrals made	Dashboard for appQCH records	Audit at completion of data collection
	**IMPLEMENTATION**		
Child/Caregiver	Acceptability, satisfaction	Structured interview	At completion of data collection
Service providers	Acceptability, satisfaction	Structured interview	At completion of data collection
QCH	Documentation of symptom burden and management	QCH records	Audit completion of data collection
QCH	Number of hospital presentations/clinical encounters	QCH records	At completion of data collection

*QCH* Queensland Children’s Hospital; *RE-AIM *[44] Reach, Effectiveness, Adoption, Implementation Maintenance

### Participants

Participants will be consecutively recruited from the Children’s Cancer Centre Day Oncology Unit by research nurses not involved in the clinical care of children. We have previously described in detail our recruitment strategies with this population group [36]. Recruitment to the control group commenced in January 2020.

### Inclusion criteria

Children aged 4 to 18 years, receiving active treatment for blood cancer or solid tumors and their caregiver/s are included. Active treatment for cancer is defined as receiving either planned cycles of chemotherapy or radiotherapy. Participants will be recruited within two weeks of a planned treatment cycle. Prior to recruitment, their clinical status and the appropriateness of approaching potential participants will be confirmed with the treating clinicians. Participants are required to be able to read and understand English, and to have access to a smartphone, iPad or computer and Internet.

### Exclusion criteria

Children with brain cancer are excluded from this study due to multiple competing studies currently being undertaken in children’s brain cancer at the cancer centre and the concern of overburdening participants. Children who are receiving Hematopoietic Stem Cell Transplantation are also excluded from the current trial due to the complexity of managing their disease and side effects. Children with advanced disease, or disease progression are excluded from the current trial. Furthermore, participants will be excluded if there is difficulty with obtaining consent (for example, the child is under child protection orders), or if there are difficulties understanding English. While inclusion of versions for non-English speaking families is ultimately our goal, this first version is developed using tools validated in the English language.

### Sample size

The sample size is based upon feasibility. Considering previous research [37], we anticipate 50 % of participants will meet the eligibility criteria (many children diagnosed with cancer are aged under 4 years) and that 80 % will consent to the study, meaning over a 12-month time period, approximately 80 participants per group can be recruited. To account for 20 % attrition, recruitment will continue until there are 96 participants in each group. In terms of clinical effectiveness, a difference of 2.7 on the SSPedi scale is considered clinically meaningful at the individual level [24]. Data from this current study will be used to calculate a sample size powered to detect clinically meaningful differences in a larger future study.

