### Control Group

The control cohort recruited during the development of the app receives usual care with no access to the RESPONSE system. Data collection for the control group commenced in January 2020 but was interrupted and paused because of COVID-19 for several months and is ongoing; recruitment will continue until the app is released and tested prior to commencing the trial.

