### Intervention group

Intervention participants will receive usual care, supplemented by symptom monitoring through completion of SSPedi, stratified alerts based upon the pre-defined algorithms, access to symptom management recommendations and graphical displays of symptom trends over time through the RESPONSE system (Fig. 1). Recruitment will continue until 1:1 matching is achieved on disease type of the recruited controls.

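### Recruiting 96 per group leaves about 77, not 80, after 20% attrition; the abstract's 160 recruited conflicts with the 192 in the main text; and each group has two recruitment end-points with no stated precedence

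*Protocol article*

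**What the plan says.** The relevant statements stand in four places in the protocol article.

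- **Sample size.** "The sample size is based upon feasibility". From an expected 50% eligibility and 80% consent, the section concludes that over 12 months "approximately 80 participants per group can be recruited". It then adds an allowance, "To account for 20 % attrition", and sets the target: "recruitment will continue until there are 96 participants in each group". No significance level, power or standard deviation is given.
- **Abstract, Methods.** "One-hundred and sixty children with cancer receiving active treatment will be recruited 1:1", in two equal groups of 80. Attrition and the figure of 96 are not mentioned.
- **Control Group.** For controls, "recruitment will continue until the app is released and tested prior to commencing the trial".
- **Intervention group.** "Recruitment will continue until 1:1 matching is achieved on disease type of the recruited controls".

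**The concern.** An allowance for attrition should be made by dividing the number wanted at the end by the proportion expected to stay. Multiplying by one plus the attrition rate gives too small a figure, and 96 looks like the result of that. A reader who takes the section at face value will expect 80 children per group to remain, and the plan's own attrition rate does not deliver that.

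The abstract and the main text also give different totals for the number recruited, so it is unclear what size of study is being reported.

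Finally, the Sample size section fixes a count for both groups, while the group-specific sections each give a different event that ends recruitment. In a non-randomised study with historical controls, the point at which recruitment ends partly decides who is compared with whom. The governing rule should therefore be known in advance.

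**Working it through.** **Inputs** (protocol article)
- New diagnoses: about 200 per year (Context and setting)
- Eligible 50%, consenting 80%, attrition 20%, target 96 per group (Sample size)
- Total recruited 160, 80 per group (Abstract, Methods)

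**1. The base of 80.** 200 x 0.50 x 0.80 = 80 per 12 months. This reproduces the plan's figure.

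**2. The target of 96.**
- Correct inflation, N / (1 - d): 80 / (1 - 0.20) = 80 / 0.80 = 100. This does not reproduce 96.
- Multiplying instead, N x (1 + d): 80 x 1.20 = 96. This reproduces it exactly.

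**3. What 96 leaves.**
- Remaining per group at 20% attrition: 96 x 0.80 = 76.8, about 77.
- Remaining in total: 2 x 76.8 = 153.6, about 154.
- Shortfall from 80: 80 - 76.8 = 3.2, about 3 per group.
- Attrition at which 96 leaves exactly 80: 1 - 80/96 = 16.7%.

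**4. Abstract against main text.** 2 x 96 = 192 recruited, against 160 recruited in the abstract, a difference of 32. Reading 160 as the number completing does not reconcile them either, because the main text's own figures give about 154.

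**5. Recruitment end-points, group by group.**

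| Group | Sample size section | Group-specific section |
|---|---|---|
| Control | 96 recruited | App released and tested |
| Intervention | 96 recruited | 1:1 disease-type matching to the recruited controls completed |

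*Controls.* If the app is ready before 96 controls are enrolled, one rule stops recruitment and the other continues it. If 96 are enrolled first, the positions reverse. The Control Group section reports a pause of several months because of COVID-19, so there is no reason to expect the two to coincide.

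*Intervention.* With 96 controls, complete 1:1 matching implies 96 matched intervention children, so the two rules agree on the final matched number. They part in two cases: if fewer than 96 controls were recruited, or if the first 96 intervention children do not have the controls' disease mix. The article does not say what happens in either case.

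**The case against.** Several points can fairly be made for the plan.

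- *The size is set by feasibility.* No power or precision is claimed, so about 3 fewer children per group breaks no stated property. This stands, and it limits the importance of the point.
- *The article does not say outright that 80 is the number to be retained.* That is an inference. It is nonetheless the reading that gives 96 a source, and it matches the 80 per group in the abstract.
- *Children who leave early still contribute.* The Effectiveness analysis section plans mixed models on repeated measures, with imputation. This stands too. The figure of 77 is the number expected to remain, not the number in the analysis.
- *The abstract may mean completers.* It may, but its verb is recruited, and the main text's figures do not yield 160 completers.
- *The recruitment rules apply to different groups.* Correct. A reader might infer three rival rules for one study. In fact there are at most two for each group, and they could coincide. What stands is that nothing says which prevails if they do not.

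A reader might also infer that the timeline is wrong, since 96 at 80 per 12 months takes 96/80 x 12 = 14.4 months. The article does not support this: it gives 12 months for about 80 and then says that recruitment continues to 96, without promising 96 in 12 months.

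A further tempting inference is that matching by disease type will force far more than 96 enrolments, or the refusal of eligible children with a distorted Reach percentage. The article defines neither the disease categories for matching nor their frequencies, and it describes no practice of turning children away. Neither the extra number nor the effect on Reach can be established from it.

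**Conclusion.** The point holds as a correction to stated figures and an unresolved precedence between recruitment limits.

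The allowance for attrition is miscalculated, and the number expected to remain is overstated by about 3 per group. The recruited total differs by 32 between abstract and main text. These results rest on two assumptions: that 80 per group is the number meant to remain, and that the 20% is the proportion of recruited children lost.

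The conflict between end-points is one of wording. The article shows that the rules can diverge, not that they have diverged.

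Materiality is modest, because no power is stated. The findings do not show that the design is undersized for a stated purpose, nor that disease-type matching is unworkable and should be abandoned. The Abstract and the Study design section define the comparison through a matched control group. Removing the matching would change the design of a non-randomised study, which these discrepancies do not justify.

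**What to change.** 1. In Sample size, state that 96 children per group (192 in total) will be recruited and that about 77 per group (about 154 in total) are expected to remain at 20% attrition.
2. In the abstract, give 192 as the number recruited, 96 per group.
3. In Control Group, state whether the count of 96 or app release governs when they differ. In Intervention group, state whether the count of 96 or completion of matching governs, and what happens if fewer than 96 controls were enrolled. Keep the 1:1 disease-type matching.

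The cost is a change of text and a slightly less favourable expected number completing, about 3 fewer per group. No stated power is affected, and neither the recruitment target of 96 nor the matched design changes.
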